### Unblinding Procedure

In this study, the Pharmacist or his/her unblinded designee will hold the subjects treatment assignment information. For medical emergencies, the Investigator will be provided with a set of numbered and sealed code-break envelopes that will contain the treatment assignment for each enrolled subject. All treatment assignment information, including code-break envelopes, must be kept in a secure location.

In a medical emergency when knowledge of the subject’s treatment assignment may affect the subject’s clinical care, the Investigator or designee may open the code-break envelope that corresponds to the subject experiencing the event (Section 15.5.5). However, prior to opening the envelope (unblinding), the Investigator or designee should attempt to contact the Biogen Idec Medical Director at Biogen Idec (see study contact information). The date and the reasons for opening the code-break envelope must be submitted to Biogen Idec within 24 hours of the unblinding. Any opened envelopes must be returned to the secure location. Code-break envelopes will be checked at monitoring visits and will be collected at the end of the study.

The Investigator must document the reasons for unblinding in the subject’s source documents. *The Investigator is strongly advised not to divulge the subject’s treatment assignment to any individual not directly involved in managing the medical emergency*

# STUDY TREATMENT description and allocation

Study treatment must be stored in a secure location. Accountability for study treatment is the responsibility of the Investigator. More details concerning this responsibility are included in Section 10.3.

Study treatment must only be dispensed by a Pharmacist or medically qualified staff. Study treatment is to be dispensed only to subjects enrolled in this study. Once study treatment is prepared for a subject, it can only be administered to that subject. Study treatment vials are for one‑time use only; any study treatment remaining in the vial should not be used for another subject.

Study site staff should refer to the Directions for Handling and Administration (DHA) located in the Study Reference Manual for specific instructions on the handling and administration of the study treatment. The DHA supersedes all other references (e.g., Investigator’s Brochure).

## <BG00010 (Neublastin) descripton redacted>

## Placebo

Saline provided by the study site will be used as placebo.

## Study Treatment Accountability

The study site must maintain accurate records demonstrating dates and amount of study treatment received, to whom dispensed (subject‑by‑subject accounting), and accounts of any study treatment accidentally or deliberately destroyed.

Unless otherwise notified, all used and unused vials must be saved for study treatment accountability. At the end of the study, reconciliation must be made between the amount of study treatment supplied, dispensed, and subsequently destroyed. A written explanation will be provided for any discrepancies. After reconciliation, the Investigator must destroy all unused vials of study treatment as instructed by Biogen Idec.

If any study treatment supplies are to be destroyed at the site, the institution/Principal Investigator must obtain prior approval by Biogen Idec. After such destruction, the institution/Principal Investigator must notify Biogen Idec, in writing, of the method of destruction, the date of destruction, and the location of destruction.

# TREATMENT

## Treatment Schedule

Eleven single-dose cohorts are planned (10 IV and 1 SC). For each cohort, 4 subjects will be randomized to receive 1 adminstration of study treatment (3 subjects will receive BG00010 and 1 subject will receive placebo).

For the dose escalation part of the study, study treatment will be administered as an IV injection by the Investigator or designee.

For the SC administration substudy, study treatment will be administered as up to 4 SC injections (depending on body weight).

BG00010 doses will be escalated according to the cohort design presented in Table 11-1.

Table 11‑2 Planned Cohorts

| **Cohort** | **BG00010 Dose**  **(g/kg)** | **Number of Doses of Study Treatment** | **Number of Subjects on BG00010** | **Number of Subjects on Placebo** |
| --- | --- | --- | --- | --- |
| A | 0.3 | 1 | 3 | 1 |
| B | 1 | 1 | 3 | 1 |
| C | 3 | 1 | 3 | 1 |
| D | 10 | 1 | 3 | 1 |
| Safety Report submitted to the Ethics Committee (Section 11.1.2) | | | | |
| E | 25 | 1 | 3 | 1 |
| F | 50 | 1 | 3 | 1 |
| Safety Report submitted to the Ethics Committee (Section 11.1.2) | | | | |
| G | 100 | 1 | 3 | 1 |
| H | 200 | 1 | 3 | 1 |
| I | 400 | 1 | 3 | 1 |
| J | 800 | 1 | 3 | 1 |
| K* | 50 (SC) | 1 | 3 | 1 |
| * Recruitment to this cohort will commence anytime after all subjects in Cohort G (100 g/kg) have completed their Day 56 visit. | | | | |

Four additional subjects will be added to an IV cohort if the DSRC requests that additional subjects be added as the result of a DSRC safety review, or if there is a clinical suspicion of a new sensory abnormality (the determination of sensory function will be made by the DSRC using clinical, neurological, QST, and IENFD data).

### Dose Suspension

The Investigator must contact the Biogen Idec Medical Director prior to dosing the next subject if a subject experiences a treatment-related increase of 4 points from baseline in one of their pain evaluations, a treatment-related SAE, or a treatment-related Grade 3 or higher laboratory AE.

Dosing of a cohort will be suspended until the DSRC completes a safety evaluation (Section 19.2). The decision to continue dosing the cohort will be based on the nature and severity of the SAE or laboratory AE (if applicable), and a review of all available safety data (AEs; all SAEs; vital signs; results for laboratory tests, Likert numerical pain rating assessments, QST, and IENFD).

Refer to Section 7.3 for Study Stopping Rules.

### Dose Escalation

Prior to enrollment into the next IV cohort (the next planned dose level), the DSRC will review unblinded safety data (AEs; all SAEs; vital signs; results for laboratory tests, Likert numerical pain rating assessments, QST, and IENFD) through Day 28, and PK data through Day 5 (or an earlier time point if the concentration drops below the limit of quantitation prior to Day 5) from all subjects in the preceding cohorts (see Section 19.2). Enrollment of the next cohort will not begin until the DSRC has approved dosing for that cohort.

If serum exposure for Cohorts A, B, or C exceeds the NOAEL, an ad hoc safety analysis will be performed, and a safety report generated from data collected for all treated Cohorts will be filed with the Ethics Committee prior to initiating dosing for the subsequent cohort.

Two interim safety analyses are planned. If serum exposure for Cohorts A, B, or C does not exceed the NOAEL, an interim safety analysis will be performed after all subjects in Cohort D have completed their Day 28 evaluations. A safety report generated from the data collected through Day 28 for Cohorts A through D will be filed with the Ethics Committee prior to initiating dosing of Cohort E. A second interim safety analysis will be completed after all subjects in Cohort F have completed their Day 28 evaluations. A safety report generated from the data collected through Day 28 for Cohorts A through F will be filed with the Ethics Committee prior to initiating dosing of Cohort G.

Safety data from the SC cohort will not be used as part of the determination for escalation of the IV dose.

## Withdrawal of Subjects From the Study

Subjects must be withdrawn from the study for any one of the following reasons:

- The subject desires to discontinue participation in this study.
- The subject is unwilling or unable to comply with the protocol.
- Other unspecified reasons that, in the opinion of the Investigator, make the subject unsuitable to continue study participation.

Subjects who prematurely withdraw from the study postdosing should be encouraged to complete the tests and evaluations for the Day 28 visit within 14 days after withdrawal from the study, as well as the Follow-Up Visit 28 days later. If the subject withdraws within 48 hours postdosing and completes the tests/assessments for the Premature Study Withdrawal Visit within those 48 hours, blood, serum, and plasma for potential biomarker analyses will also be collected. Subjects who prematurely withdraw postdosing may not be replaced. However, subjects who prematurely withdraw prior to dosing may be replaced. The reasons for the subject’s withdrawal from the study must be recorded in the subject’s Case Report Form (CRF).

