## Dose Rationale

The dose and dosing schedule are based on 2 factors: (a) the 13-week toxicology results, and (b) the projected efficacious human dose.

The 13-week toxicology study performed in non-human primates showed a No Observed Adverse Effect Level (NOAEL) of 4000 g/kg IV. No adverse events were observed in non-human primates at this dose and it was the highest dose tested. This dose is anticipated to scale to a human equivalent dose (HED) of 1300 g/kg based on body weight/surface area calculation. The clinical safety margin for the starting human dose of 0.3 g/kg is 4300-fold.

Allometric scaling was performed with IV doses from rat and monkey data, and exposure estimations from SC efficacy studies performed in rats. A conservative estimate of 10% bioavailability from SC pharmacology studies in rats predicted possible efficacious human dose starting at 37 g/kg. Therefore, a starting dose of 0.3 g/kg represents approximately 1/100 of a predicted possible efficacious dose.

The selected upper IV dose limit of 800 g/kg would provide a minimum 1.6-fold safety margin based on the NOAEL.

Initially, IV dose cohorts will increase by half-log increments. In IV dose cohorts beyond 10 g/kg (i.e., at doses approaching the projected efficacious dose) dose escalation will proceed in smaller increments. All subject exposures will be limited to a single dose. Based on the PK of BG00010 in animals, the concentration is expected to drop below the bioanalytical quantification limit (0.1 ng/mL) within 6 days.

Based on the exposure estimations from SC efficacy studies performed in rats SC, a dose of 50 g/kg should represent a dose at which BG00010 levels can be detected in the serum and can therefore determine bioavailability relative to IV administration.

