## Concomitant Therapy and Procedures

A concomitant therapy is any drug or substance, including nonprescription drugs, herbal preparations, and vitamins, administered from the Screening Visit until the Follow-Up Visit (Day 56).

Concomitant treatment with narcotic and non-narcotic analgesics, acetaminophen (not to exceed 4 g/day), non-steroidal anti-inflammatory drugs, aspirin, and over-the-counter products such as vitamins or mineral supplements is allowed if the dosing of these medications/supplements has been stabilized prior to the Baseline Visit and remains stable throughout the study. Concomitant treatment with previously prescribed TCAs, SSRIs, and SNRIs is allowed if the dosing of these medications has been stable for 4 weeks prior to the Baseline Visit and remains stable throughout the study. Concomitant treatment with gabapentin and pregabalin is allowed if the dosing of these medications has been stable for 1 week prior to the Baseline Visit and remains stable throughout the study.

Subjects should be instructed not to start taking any new medications, including nonprescription drugs and herbal preparations, unless they have received permission from the Investigator.

A concomitant procedure is any therapeutic intervention (e.g., surgery/biopsy, physical therapy) or diagnostic assessment (e.g., blood gas measurement, bacterial cultures) performed from the Screening Visit until the Follow-Up Visit, unless the subject is being followed for study‑related toxicity.

The use of concomitant therapies or procedures defined above must be recorded on the subject’s CRF, according to instructions for CRF completion. AEs related to administration of these therapies or procedures must be documented on the appropriate CRF.

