## Safety Data

### Analysis Population

The safety population is defined as all subjects who are randomized and have been dosed with study treatment.

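### Section 11.2 requires dosed subjects who do not comply to leave the whole study, which after a single dose only curtails safety follow-up and leaves adverse-event recording contradictory

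*Protocol*

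**What the plan says.** Protocol Section 11.2 opens its list with "Subjects must be withdrawn from the study for any one of the following reasons", and one of the three reasons is "The subject is unwilling or unable to comply with the protocol". Neither sentence refers to dosing. Later in the same section, dosing status is used to decide replacement: "Subjects who prematurely withdraw postdosing may not be replaced", whereas those leaving before dosing may be.

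Section 5.5 states that "All subject exposures will be limited to a single dose", and Section 11.4 provides no further courses.

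After withdrawal, Section 11.2 asks only that the subject be encouraged to complete the Day 28 assessments within 14 days and the Follow-Up Visit 28 days after that. Sections 14.2.11 and 14.2.12 add that this is to happen if possible.

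Sections 15.2.2 and 15.2.3 and Figure 15-1 end the recording or reporting of adverse and serious adverse events at Day 56 or at premature withdrawal. Section 14.2.12 includes event monitoring in its Follow-Up Visit list, and that list is also meant for withdrawn subjects.

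Section 11.3 permits analgesics and supplements on the condition that dosing "has been stabilized prior to the Baseline Visit and remains stable throughout the study", with similar conditions for antidepressants, gabapentin and pregabalin. New medicines may be started only with the Investigator's permission.

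Section 16.4.1 says: "The safety population is defined as all subjects who are randomized and have been dosed with study treatment".

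**The concern.** The objective is the safety, tolerability, pharmacokinetics and immunogenicity of one administration in everyone who received it. In a multiple-dose study, withdrawal for non-compliance can at least end exposure. Here, once Day 0 has passed, there is nothing left to stop, so the rule acts only on observation.

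Three things are at stake.

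- **Completeness for dose escalation.** Sections 11.1.2 and 19.2 have the Drug Safety Review Committee review safety data through Day 28 and PK data through Day 5 from all subjects in the preceding cohorts. A withdrawn subject may not supply these data, or may supply the Day 28 assessments too early.
- **Adverse events after withdrawal.** The text gives two answers on whether they are recorded.
- **Bias.** Pain is a primary safety endpoint, and a subject in more pain is the one more likely to depart from the stable-dosing condition in Section 11.3. If that departure is treated as non-compliance, the loss depends on the outcome.

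**Working it through.** **1. The plan's own figures.** There are 11 cohorts, 10 IV and 1 SC. Minimum: 11 × 4 = 44. Maximum: 10 × 8 + 1 × 4 = 84. Both agree with Section 9.1. Section 16.8 gives no power basis, so no power figure is affected. Each block of 4 subjects has 3 on active drug.

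**2. Share lost.** One withdrawn active subject is 1/3 = 33% of the active group in a base cohort and 1/6 = 17% in an expanded one.

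**3. When the encouraged visits fall.** For withdrawal on Day w, the latest date for the Day 28 assessments is w + 14, and the latest Follow-Up Visit is w + 14 + 28 = w + 42.

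| Withdrawal day | Day 28 assessments by | Follow-Up Visit by |
| --- | --- | --- |
| 3 | Day 17 | Day 45 |
| 7 | Day 21 | Day 49 |
| 14 | Day 28 | Day 56 |

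The Day 28 window of -2 to +5 days is Day 26 to Day 33. The assessments fall before it whenever w + 14 < 26, that is, w < 12.

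In the Study Activities table, IENFD has one postdose assessment (Day 28), QST has two (Days 1 and 28), and antibody sampling has two (Days 21 and 28). Early withdrawal therefore either loses the only postdose IENFD or moves it forward.

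**4. Adverse-event recording, side by side.**

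| Section | Recording for a withdrawn subject |
| --- | --- |
| 15.2.2 and 15.2.3 | Ends at premature withdrawal |
| Figure 15-1 | Reporting of serious events ends at premature withdrawal |
| 14.2.12 | Event monitoring is listed at the later Follow-Up Visit |

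Even if premature withdrawal is read as the withdrawal visit rather than the decision to withdraw, recording would close up to four weeks before a visit that asks for it.

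**5. Illustration of detection.** The true event rates p are assumptions, because the protocol gives none. Exactly one active subject is assumed lost, with no later data, and the loss is assumed independent of the event. The chance of seeing at least one later event among n active subjects is 1 - (1 - p)^n.

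| p | n = 3 | n = 2 |
| --- | --- | --- |
| 10% | 1 - 0.9³ = 0.271 | 1 - 0.9² = 0.190 |
| 20% | 1 - 0.8³ = 0.488 | 1 - 0.8² = 0.360 |
| 33% | 1 - 0.67³ = 0.699 | 1 - 0.67² = 0.551 |

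In an expanded cohort at 20%, the chance falls from 1 - 0.8⁶ = 0.738 to 1 - 0.8⁵ = 0.672.

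The sensory stopping rule in Section 7.3 needs 2 affected subjects. At 20%, the chance of 2 or more falls from 3 × 0.2² × 0.8 + 0.2³ = 0.104 to 0.2² = 0.040.

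**The case against.** Much can be said for the plan as written.

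- **Follow-up is not abolished.** Withdrawn subjects are asked to attend the full Day 28 assessments and a later visit. Section 15.2.3 has serious events that are ongoing at discontinuation followed until they resolve, stabilise or return to baseline. Every subject has at least 48 hours of inpatient observation. This stands: follow-up becomes shorter and voluntary, but it does not end.
- **Analgesic change.** A reader might infer that a subject who changes analgesics must be withdrawn. The protocol does not say so. Being unwilling or unable to comply is a matter of judgement, and exclusion criterion 8 under Miscellaneous in Section 8.2 links similar words to attendance at visits. Section 15.3.2 foresees that a subject with a moderate event may need treatment and still continue. Section 11.3 bars new medicines "unless they have received permission from the Investigator", which makes some changes compliant, although it does not expressly cover a dose change in an existing medicine. Outcome-related loss is therefore possible but not mandated.
- **Lost pain signal.** A reader might also infer that a pain signal disappears. If one of three active subjects rises by 4 points and two do not change, the mean is (4 + 0 + 0)/3 = 1.33; without that subject it is 0. This holds only for means at later visits, with no return. Ratings before withdrawal stay in the all-dosed safety population, and a treatment-related 4-point rise in one subject suspends dosing under Section 11.1.1.
- **Stopping rules.** Only the sensory rule counts 2 subjects. The serious-event and laboratory rules count events, and none is a pain rule.
- **Limits of wording.** No text can keep a subject who refuses further visits.

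What the objection leaves untouched is the mandatory wording for dosed subjects and the contradiction on event recording.

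**Conclusion.** The point holds in a limited form. After the only dose, mandatory withdrawal for non-compliance protects no one from further exposure. It makes later safety assessments voluntary, can bring them forward, and leaves event recording contradictory. The contradiction and the visit dates follow from the text alone.

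The size is up to 1 of 3 active subjects missing from later assessments in a base cohort, for each such withdrawal. Under an assumed 20% event rate, with that subject giving no later data, the chance of seeing at least one later event in the cohort falls from 49% to 36%. The loss is smaller if the subject attends the encouraged visits. Outcome-related bias is a plausible route whose frequency the protocol does not allow one to estimate. The documents do not support saying that an analgesic change compels withdrawal, or that data already collected are lost. The change is worth making because it is cheap and each cohort is so small.

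**What to change.** In Section 11.2, keep mandatory withdrawal for non-compliance for subjects not yet dosed. For dosed subjects, record non-compliance as a protocol deviation, and continue the scheduled safety assessments and adverse-event recording to Day 56 unless the subject withdraws consent. The Investigator-discretion reason can stay; removing it is debatable and not needed for this change.

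Reconcile Sections 11.2, 11.3, 14.2.12, 15.2.2 and 15.2.3 and Figure 15-1, so that they give one answer on how long events are recorded for a subject who leaves early and on how departures from the concomitant-therapy conditions are classified. No rule on analgesic use is proposed.

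The cost is one paragraph in an amendment plus aligned wording elsewhere. The visits are already in the schedule. The small downside is that some pain ratings will be taken under changed concomitant therapy and will need a flag in the listings.

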## Concomitant Therapy and Procedures

A concomitant therapy is any drug or substance, including nonprescription drugs, herbal preparations, and vitamins, administered from the Screening Visit until the Follow-Up Visit (Day 56).

Concomitant treatment with narcotic and non-narcotic analgesics, acetaminophen (not to exceed 4 g/day), non-steroidal anti-inflammatory drugs, aspirin, and over-the-counter products such as vitamins or mineral supplements is allowed if the dosing of these medications/supplements has been stabilized prior to the Baseline Visit and remains stable throughout the study. Concomitant treatment with previously prescribed TCAs, SSRIs, and SNRIs is allowed if the dosing of these medications has been stable for 4 weeks prior to the Baseline Visit and remains stable throughout the study. Concomitant treatment with gabapentin and pregabalin is allowed if the dosing of these medications has been stable for 1 week prior to the Baseline Visit and remains stable throughout the study.

Subjects should be instructed not to start taking any new medications, including nonprescription drugs and herbal preparations, unless they have received permission from the Investigator.

A concomitant procedure is any therapeutic intervention (e.g., surgery/biopsy, physical therapy) or diagnostic assessment (e.g., blood gas measurement, bacterial cultures) performed from the Screening Visit until the Follow-Up Visit, unless the subject is being followed for study‑related toxicity.

The use of concomitant therapies or procedures defined above must be recorded on the subject’s CRF, according to instructions for CRF completion. AEs related to administration of these therapies or procedures must be documented on the appropriate CRF.

## Continuation of Treatment

There is no provision for additional courses of BG00010 provided by Biogen Idec beyond the treatment defined in this protocol.

# Safety Assessments

## Clinical Safety Assessments

The following clinical assessments will be performed to assess the safety profile of BG00010:

- complete physical examinations
- measurement of vital signs (including systolic and diastolic blood pressure, pulse, and body temperature)
- clinical neurological examinations including a motor examination, a deep tendon reflex examination, and a sensory examination (joint position sensation, vibration sensation, pinprick sensation, and temperature sensation)
- numerical pain rating assessments as measured by an 11-point Likert scale(Likert, 1952)
- ECG (12-lead)
- longitudinal assessment of QST (Vibratory, Cool Thermal, and Heat Pain thresholds)
- punch biopsy (IENFD)
- monitoring of AEs, SAEs, and concomitant therapy.

